## Abstract

**Background:**

Quality improvement networks are peer-led programmes in which members of the network assess the quality of care colleagues provide according to agreed standards of practice. These networks aim to help members identify areas of service provision that could be improved and share good practice. Despite the widespread use of peer-led quality improvement networks, there is very little information about their impact. We are conducting a cluster randomized controlled trial of a quality improvement network for low-secure mental health wards to examine the impact of membership on the process and outcomes of care over a 12 month period.

**Methods:**

Standalone low secure units in England and Wales that expressed an interest in joining the quality improvement network were recruited for the study from 2012 to 2014. Thirty-eight units were randomly allocated to either the active intervention (participation in the network *n* = 18) or a control arm (delayed participation in the network *n* = 20). Using a 5 % significance level and 90 % power, it was calculated that a sample size of 60 wards was required taking into account a 10 % drop out. A total of 75 wards were assessed at baseline and 8 wards dropped out the study before the data collection at follow up. Researchers masked to the allocation status of the units assessed all study outcomes at baseline and follow-up 12 months later. The primary outcome is the quality of the physical environment and facilities on the wards. The secondary outcomes are: safety of the ward, patient-rated satisfaction with care and mental well-being, staff burnout, training and supervision. Relative to control wards, it is hypothesized that the quality of the physical environment and facilities will be higher on wards in the active arm of the trial 12 months after randomization.

**Discussion:**

To our knowledge, this is the first randomized evaluation of a peer-led quality improvement network that has examined the impact of participation on both patient-level and service-level outcomes. The study has the potential to help shape future efforts to improve the quality of inpatient care.

**Trial registration:**

Current Controlled Trials ISRCTN79614916. Retrospectively registered 28 March 2014]

## Background

Quality networks aim to enhance standards of health care by engaging and supporting clinicians and managers to assess and improve the quality of the care they provide [1]. By assessing quality of care against recommended standards and providing feedback on service quality to front-line staff, quality networks have much in common with accreditation schemes. However, in quality networks services do not work towards achieving accreditation for the care they provide. Rather, they receive suggestions and support for initiating changes to services and to keep front-line staff engaged in efforts to improve service quality. Over recent years the number of quality networks and accreditation programmes has substantially increased [2]. Despite this, there is little evidence to judge how effective they are, and the impact they have on patient outcomes is largely unknown.

Data from observational studies of services that participate in quality networks show that they achieve higher standards of care over time [3–5]. However, comparative data from services that do not take part in such networks have rarely been gathered. A greater amount of research has been conducted into the impact of accreditation programmes. A systematic review of the impact of accreditation programs found some evidence from observational studies that such programmes improve staff perceptions of service quality [6]. Consistent findings about impact on patient outcomes were not found.

To date, two randomized controlled trials have been carried out to explore whether peer-led quality improvement programs enhance the quality of patient care [7, 8]. The first study was conducted in acute hospitals in KwaZulu-Natal, South Africa. Over the course of two years, greater improvements in standards of care were seen in hospitals that were randomized to participation in an accreditation programme. However, differences in clinical records keeping, hospital sanitation and patient satisfaction with care were not found. While this study demonstrated that experimental studies of peer-led quality improvement initiatives are feasible, its limitations, including a small sample size and inconsistent implementation of the accreditation programme limits generalisability to other clinical settings. In addition, hospitals that were randomized to control treatment appear to have had limited exposure to other quality improvement initiatives. In Europe, North America and other industrialised economies health services are usually involved in a range of other quality improvement initiatives, such as local audits or statutory inspection. In this context, Roberts and colleagues [8] conducted a randomized trial to explore the added value of participation in a peer-led quality improvement initiative in the United Kingdom. In this study, hospitals admitting patients with acute Chronic Obstructive Pulmonary Disease (COPD) were randomized to the intervention arm of the trial that received a reciprocal peer-review and a control arm that continued to undertake COPD service development within normal processes. A number of quality indicators drawn from national guidelines were used to measure service outcomes as well as four key areas of service provision. Participating services had to complete a self-assessment baseline pro-forma describing the service provision and attainment (met in full, partially met, not met at all) of the quality indicators. This document was used to direct discussions and record observations during the peer-review visit. After each peer-review visit, the intervention units received a final report and agreed action plans for service development. All services were asked to complete a change diary 12 months after all the peer-review visits were completed to provide information about major service changes occurring during the year that could be related to their involvement in the study or not. Follow-up data at 12 months on those aspects of care assessed at baseline were collected as part of the UK National COPD Audit. The results showed that the compliance of the services in the intervention group with the quality indicators assessed was only marginally higher than that shown by the control group. In contrast, qualitative data suggested many benefits of the peer-review in most intervention units and some control teams [8]. One limitation of this study was that the data collected at baseline relied entirely on the services’ self-assessment. In addition, the team did not assess whether the peer review process had any impact on patients’ experience of their care.

The Royal College of Psychiatrists’ Centre for Quality Improvement runs a range of peer-led quality improvement programmes (see: http://www.rcpsych.ac.uk/researchandtrainingunit/centreforqualityimprovement.aspx). The setting up of a new quality improvement network starts with the development of service standards that are based on recommendations made by professional bodies and organisations such as the National Institute for Health and Clinical Excellence [9, 10]. Front-line clinicians and service users and carers are all involved in the development of these standards. Services that choose to participate in a network are sent materials necessary to conduct a self-review (where they indicate whether they believe that they meet or do not meet agreed standards of care). The self-review is followed by an independent assessment led by a multi-professional team of trained peers who work in similar clinical settings. Service users and carers also take part in these assessments [1]. Discrepancies between the self-review and the peer review data are discussed and feedback on service quality is then provided to each service after each visit. Clinical teams are sent a final report summarising the services’ achievements and areas of improvement and are supported to develop an action plan aimed at making improvements to service quality. Participation in a quality network also offers access to online discussion groups, newsletters, workshops and an annual forum. These activities encourage services to share good practice and find solutions to the challenges they share.

Essentially, network membership entails committing to a culture of openness, sharing and enquiry through a supportive peer-led process with the common goal for all members to improve quality of care. All members are required to engage actively in all stages of the peer-review cycle (self-review, peer-review, attendance of annual forum) and expected to use the results of reviews to develop action plans to achieve year on year improvement. Members are also expected to share their results throughout their services as well as with key stakeholders, including health and local authorities, those making referrals to their services and local patient and carer groups.

Secure inpatient forensic mental health units are specialist services for people with mental health problems who have either committed a criminal offence or whose challenging behaviour requires a level of security that is higher than that provided in mainstream adult mental health services. They are called ‘secure’ because the freedom of people treated on these units is restricted by mental health legislation. Inpatient forensic mental health services aim to treat people’s mental health problems and ensure the safety of patients and the public by monitoring risk, preventing absconsions and providing support and supervision while on the unit and on agreed periods of leave. When the decision was made to set up a new peer-review network for low secure inpatient forensic units, we built in a randomized evaluation in which low secure units were randomly allocated to immediate or delayed participation in the quality network 12 months later. The low-secure network aims to help individual services identify areas where their practice falls below national standards and to share good practice aimed at improving the quality of care they provide. The standards used in the network cover key aspects of physical and relational security, the interventions and treatments patients are offered, the quality of the physical environment, training, supervision and support for staff the governance of services including the way that adverse incidents are reported and managed. We hypothesised that through helping teams focus on these areas of care, membership of the network would help them identity where these elements of care could be improved and that this in turn would impact on the health, well-being and experience of the patients treated on these units.

### Aim of the study

The aim of the study is to assess the impact of membership of the quality improvement network for Low Secure Units on the quality of care that people receive.

### Hypotheses

The primary hypothesis is that the quality of the physical environment and facilities in wards that participate in the network will be higher 12 months after randomization than in those wards that do not participate.The secondary hypotheses are that, 12 months after randomization, wards that participate in the network will have:i)Higher levels of safetyii)Higher levels of patient satisfactioniii)Higher levels of patient mental well-beingiv)Lower levels of staff burnoutv)Higher levels of training and supervision for staff

## Methods

### Trial design

The study is a two-armed, parallel group, researcher-masked, randomized controlled trial of early or late participation in a quality network. Units randomized to late participation in the network had the opportunity to join the network once all follow-up data were collected 12 months after randomization.

### Study setting and sample

Between June 2012 and June 2014, 108 low secure units were recruited to join the low secure quality network. Seventy of these units were ineligible for the study because either a) were located on the same premises as Medium Secure Forensic units that already participate in a quality network for these services (*n* = 46) or b) joined the network before the study was set up (*n* = 24). The reason to exclude the combined sites was to avoid that some staff employed across both sets of units may already have implemented changes based on their experience of the medium secure network. From the initial sample, 38 standalone units were eligible for the study and agreed to take part in the randomised trial. To minimise cross-level contamination between control and treatment group, only the members of the network could have access and share resources on the quality network website within a password protected area. The networks’ newsletters and the annual reports were made available online only after all the data collection for the whole study was completed (see Fig. 1)

**Fig. 1 Fig1:**
[figure not shown]
CONSORT 2010 Flow Diagram

.

### Study interventions

#### The quality improvement network for low secure inpatient mental health units

Standards for the network were developed by the Quality Network for Forensic Mental Health Services team (QNFMHS) directly from the ‘Low Secure Services: Good practice commissioning guide consultation draft Department of Health [11]. Some standards from the ‘Implementation Criteria for Recommended Specification: Adult Medium Secure Units’ [9] were also included. To finalise the development of the standards, the Quality Network team consulted an expert standards steering committee comprising commissioners, providers and ex-users of forensic mental health services regarding clarity, measurability and importance. In addition, a final and wider standard consultation conference was held where experts in forensic mental health (including service user representatives and carers) provided further feedback on the standards. This feedback was then incorporated in the final version of the document [12]. Forming the foundation of the iterative annual review cycle, the standards provide an accessible way for services to actively engage in on-going service development towards implementing the Department of Health recommendations. These standards form the basis of the self-review that all wards in the active arm of the trial were asked to undertake at the start of the review cycle. Having completed a self-review, arrangements were made for all services to be visited for a peer-review. Peer-reviewers were recruited from staff working in the service members, and all lead reviewers were provided with a lead reviewer training prior to their first visit. This training was delivered by the Forensic Quality Network team. At the peer-review visit, each service is required to i) arrange for the review team to be escorted for a tour of the service to assess the patients’ facilities ii) organise service users interviews, iii) provide the documentation for a service policy check in relation to the aspects of care covered in the standards, iv) organise 3 separate staff meetings with senior managers, the multidisciplinary team (MDT) and front line staff. At the end of the visit, the review team provides feedback to managers and staff representatives to highlight discrepancies between the self-assessment and the peer-review data, the service’s achievements as well as areas that need improvements. After the peer-review stage, each service is provided with a local report that compiles self and peer-review data and shows the extent to which the service meets the standards.

When all member services have completed the peer-review phase, an annual national report of the aggregated findings is written to enable benchmarking with other services and reflect on their practice. The final stage of the programme involves action planning, an invitation to an annual forum and access to newsletters and an e-mail discussion group. At the annual forum members of the network have an opportunity to hear about challenges faced by similar units and share examples of how different units have tried to meet these challenges. All the material produced by the network (e.g., annual reports, newsletters) is made available to members via a password-protected webpage.

#### Control treatment

Aside from participating in the network 12 months after randomization, all wards in the control arm of the trial were free to carry out any other quality improvement initiatives as per normal. Data about all quality improvement initiatives that wards used in the 12 month follow up period were collected. These may include local reviews, audits and the possibility of inspection by statutory bodies. Twelve months after randomization, all control wards were invited to join the quality network once all follow-up data had been collected.

#### Fidelity to active treatment

During the review cycle, the managers who co-ordinated the forensic quality network monitored the involvement in the network of all units in the active arm of the trial. This involvement included: i) two or more members of staff attending reviewer training, ii) completion of the self-review workbook at least six weeks before the date of the peer-review visit, iii) completion of a peer-review visit according to timetable, iv) participation in discussion groups and v) attendance by one or more members of staff at the annual forum.

### Measures

#### Primary outcome measure

The primary outcome was the quality of the physical environment and facilities on the wards which was assessed using a validated ‘environmental checklist’ named the QELS (Quality of Environment in Low secure Services). The QELS checklist assesses 10 domains of quality of care and generates a score between zero and 100, with higher scores indicating a higher quality of service provision relative to the physical environment (see text Table 1) [11]. Tests of the psychometric properties of the environmental checklist have shown that it has good inter-rater reliability and concurrent validity. The checklist was completed by a member of the research team who visited each ward to collect the study data. During these visits the researcher was always masked to allocation status of the unit (see randomization and blinding section for details).

**Table 1 Tab1:** Items of the QELS checklist

1. Whether the service has an external perimeter that meets the standards for security.	
2. Whether there are separate, accessible and appropriately furnished facilities for visitors.	
3. Whether all visitors, staff and patients access the ward via airlock.	
4. Whether there are any ligature points on the ward.	
5. Whether the ward has a multi-faith room accessible and appropriate for use by all patients.	
6. Whether the ward has an up to standards seclusion room.	
7. Whether the ward has a de-escalation room.	
8. Whether patients’ bedrooms are designed to maintain safety.	
9. Whether there is a variety of recreational facilities accessible to patients.	
10. Whether there is a variety of occupational facilities accessible to patients.	

#### Secondary outcome measures

i)Safety of the wards was assessed by the visiting researcher who interviewed the manager of each ward and collecting data on: number of absconsions and untoward incidents during the previous 6 months [13], proportion of patients and staff who reported being assaulted in the previous 3 months and patient and staff experience of feeling safe on the ward.ii)Service user satisfaction with care was assessed using a modified version of the Patient Satisfaction Questionnaire (PSQ) [14]. The questionnaire was modified with the approval of the team that designed the measure by changing one item to make it suitable for assessing patient experience of satisfaction with inpatient treatment (the item on “satisfaction with the place and time of the appointments” was changed to” satisfaction with the place you live” (e.g., bedroom, common areas). This questionnaire was embedded in a patient survey used in the study which included also questions on the patients’ access to community services and involvement in planning the care they receive. The patient survey was administrated by the visiting researcher on site with the help of staff members when needed to facilitate engagement with the patients.iii)Mental wellbeing of patients on wards was assessed using the Short Warwick-Edinburgh Mental Well-being Scale (SWEMWBS) [15] which was also embedded in the patient survey. The SWEMWBS was used in this study because of its brevity and robust psychometric properties [15].iv)Staff burnout was measured using the Maslach Burnout Inventory (MBI) [16, 17]. The MBI is a leading, validated measures of burnout used extensively in human services, education and business. This survey consists of 22 items that create three general subscales assessing: emotional exhaustion, depersonalization and personal accomplishment. Numerous psychometric analyses showed that the scale has both high reliability and validity as a measure of burnout [18]. The MBI was included in a staff survey used in the study which was distributed to staff to complete by the visiting researcher.v)Staff members on the ward were asked to indicate the extent to which the training and the supervision they receive was adequate to carry out their job. These questions were included in the staff survey distributed by the researcher.

### Study procedures

#### Recruitment and consent procedures

The recruitment of the low secure units was carried out by the Quality Network for Forensic Mental Health Services team who publicised the study on the network’s website. Recruitment took place over three years as part of an annual cycle of recruitment, self-review and peer review between June 2012 and June 2014. At the beginning of each peer-review cycle, the eligible units that agreed to take part in the network were randomized to the active or control arm of the trial (see study setting and sample section for details on eligibility). Thirty-eight units in total took part in the study (75 wards). Each unit nominated a link person to communicate with the research team to arrange the data collection visit. The link person was in charge of circulating the study information sheet to staff and patients at least two weeks prior the data collection visit by the researcher and coordinate the logistic of the visit between the researcher, staff and patients on the wards. The researcher was escorted by staff members on the day of the visit to observe the wards’ facilities and complete the environmental checklist. During the escorted visit the researcher engaged with staff and patients by providing further details about the study and sought informed consent to complete the study survey from those who were willing to participate. The patients who agreed to participate were assisted by the researcher or staff to fill in their survey if needed. In order to maximize completeness of data collection, the research team made every effort to monitor participants’ retention from baseline to follow-up. Retention strategies included consistent and frequent contact of the research team with service in preparation for the data collection visits.

#### Randomization and blinding

Some wards were part of a unit that included other wards on the same site. While there may be differences in services provided by different wards on the same unit, management is often shared and we judged that there was considerable potential for contamination of the effects of the intervention across wards on the same unit. We therefore randomized units rather than wards. The Quality Network team emailed the contact details of eligible services to an independent team based at Imperial College London which was in charge of the randomization process. This team used a web-based randomization programme and a randomization ratio of 1:1, early versus delayed participation in the network. Randomization was stratified according to the size of the unit (whether they contained up to four, or more than four wards). Following randomization of the 38 eligible units, 18 (47 %) were allocated by the independent team to the active arm and 20 (53 %) to the control arm of the study. The list of early and late participation units was then sent back to the Quality Network team that informed the units of their membership status.

Once all the units were informed of their allocation status, the quality network team sent the research team the full list of units enrolled for the study without any reference to their group membership. The research group then made contact with the units and arranged for baseline data collection. The units’ link person and all staff members were repeatedly reminded that the researcher collecting study data must not be told which arm of the trial they were in. In the event of accidental unmasking of a researcher, all further data were collected by a second researcher who was masked to the allocation status of the unit.

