#### Sample size

The sample size for the study was based on the primary hypothesis: the quality of the physical environment and facilities in wards that participate in the network would be higher 12 months after randomization than in those wards that do not participate in the network. A previous investigation with medium secure wards that took part in the quality network showed an increase in the proportion of standards met equivalent to a 10 % increase during the first year of membership of the network [19].

Assuming no change in outcome in the control arm, the sample size was based on detecting a 10 % difference between groups, equivalent to 10 units of the environmental checklist score. The sample size was calculated assuming an ANCOVA analysis, with the baseline scores used as the covariate. Based on preliminary data, a correlation of 0.53 between baseline and outcome scores was assumed. A standard deviation of 13.3 for the primary outcome was assumed (estimated using baseline data from the first 32 wards that took part in the trial). Using a 5 % significance level and 90 % power, it was calculated that 54 wards were required (27 in the active arm and 27 in the control arm of the trial). To take account of 10 % drop out from the study, we increased the sample size to 60 wards.

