#### Data management and analysis

All data were entered electronically into a database. Once data collection was completed, 100 % of the scores of the primary outcome measure were double checked against source data for accuracy. All analysis will follow the intention-to-treat principle. Descriptive analyses including tables and graphs of baseline organisational processes and clinical outcomes will be produced for each of the two arms of the trial.

The scores of the primary outcome measure (QELS checklist scores at 12 months) will be compared between the two groups using analysis of covariance (ANCOVA). The scores at 12 month will be considered as the outcome measure, with the wards’ scores at baseline used as a covariate.

The scores of the secondary outcome variables measured at the ward level and on continuous scales (e.g., number of untoward incidents), will be analysed using the unpaired *t*-test or Mann–Whitney test depending on the data distribution. Most secondary outcome variables are measured at the staff or patient level (e.g., staff burnout, service users mental wellbeing and satisfaction with care). It is anticipated that there will be clustering of outcomes as a result of participants receiving interventions on different wards. Such clustering violates the assumption that observed outcomes of participants are independent and can result in increased standard errors [20, 21]. To take account of this, these outcomes will be analysed using a two level multilevel regression models with patients/staff at level one and the wards as the second level. When measured, baseline values of each outcome will be used as a covariate in the analysis. Additional exploratory analysis will investigate possible predictors of the primary outcome (environmental checklist scores at 12 months). This analysis will be performed using multiple linear regression.

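### Unit size stratified the randomisation, but neither the primary ANCOVA nor any stated secondary analysis adjusts for it: a small loss of precision that costs one degree of freedom to remove

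*Protocol article*

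**What the plan says.** All references are to the Methods of the protocol article.

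- **Randomization and blinding.** The allocated entity is the unit: "We therefore randomized units rather than wards". One stratification factor is declared, with two levels: "Randomization was stratified according to the size of the unit (whether they contained up to four, or more than four wards".
- **Recruitment and consent procedures.** Allocation was done in annual batches: "At the beginning of each peer-review cycle, the eligible units that agreed to take part in the network were randomized". This gives the timing. The article does not list cycle as a stratification factor.
- **Data management and analysis, primary outcome.** QELS scores "will be compared between the two groups using analysis of covariance (ANCOVA"). The model is then specified: "The scores at 12 month will be considered as the outcome measure, with the wards’ scores at baseline used as a covariate". No other covariate is named.
- **Sample size.** The same model is assumed: "The sample size was calculated assuming an ANCOVA analysis, with the baseline scores used as the covariate".
- **Data management and analysis, secondary outcomes.** Continuous ward-level outcomes go to an unpaired t-test or a Mann–Whitney test. Staff- and patient-level outcomes go to two-level models with wards as the upper level and the baseline value, where measured, as covariate. Unit size appears in neither.

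**The concern.** A factor used to restrict the randomisation normally belongs in the analysis. Restricting allocation within strata makes the arms more alike on that factor than simple randomisation would. If the factor also predicts the outcome, the treatment estimate varies less than an analysis without the factor assumes. The between-stratum variation stays in the error term, the standard error is too large, and some of the benefit of stratifying is lost.

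A link between unit size and QELS is plausible. Several checklist items (visitors' facilities, multi-faith room, recreational and occupational facilities) could depend on the scale of the site. That is inference, since the article gives no data by stratum.

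The article does more than stay silent on covariates. It states the primary model with its covariate, repeats that covariate in the sample-size section, and names two-sample tests that have no place for a stratum term.

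**Working it through.** **1. The plan's own figure.** Inputs from the Sample size section: difference 10 points, SD 13.3, baseline–outcome correlation 0.53, 5% significance (taken as two-sided), 90% power.

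- Residual SD = 13.3 × √(1 − 0.53²) = 11.28.
- Wards per arm = 2 × (1.960 + 1.282)² × 11.28² / 10² = 26.7, so 27 per arm and 54 in total.
- With 10% dropout: 54 / 0.90 = 60.

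Both stated figures reproduce. The calculation contains no stratum term, and adding one to the analysis does not make either figure wrong.

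**2. What the term costs and gains at 54 wards.** Noncentral-t power with the residual SD above. R² is the share of residual variance that unit size explains; its values are assumptions.

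| Model | Residual df | R² | Power |
|---|---|---|---|
| Baseline only | 51 | – | 89.2% |
| Baseline + unit size | 50 | 0 | 89.2% |
| Baseline + unit size | 50 | 5% | 90.6% |
| Baseline + unit size | 50 | 10% | 92.0% |
| Baseline + unit size | 50 | 20% | 94.6% |

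The degree of freedom costs about 0.02 percentage points (89.17% to 89.15%).

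**3. Direction of the error if the term is left out.** Suppose the arms are fully balanced on unit size and wards are independent. The unadjusted standard error is then too large by a factor 1/√(1 − R²), and the true type I error is 2 × [1 − Φ(1.96/√(1 − R²))]:

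- R² = 5%: threshold 2.011, type I error 4.4%
- R² = 10%: threshold 2.066, type I error 3.9%
- R² = 20%: threshold 2.191, type I error 2.8%

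The error is on the conservative side throughout.

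**4. Illustrative simulation.** Assumed set-up: 38 units, 36 of them with one to three wards and two with five (about 82 wards); allocation balanced within size stratum; no clustering; true effect of 0.6 residual SD for power; 4,000 null and 2,000 power replicates.

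| Size effect (residual SD) | Type I, baseline only | Type I, + size | Power, baseline only | Power, + size |
|---|---|---|---|---|
| 0 | 5.6% | 5.6% | 77.4% | 77.4% |
| 0.5 | 4.0% | 4.3% | 76.0% | 77.1% |
| 1 | 4.0% | 4.8% | 71.5% | 75.9% |

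Monte Carlo standard error is about √(0.05 × 0.95/4000) = 0.3 points for type I error and about √(0.75 × 0.25/2000) = 1.0 point for power. The type I differences should therefore be read with step 3. An effect of one SD with 10 of 82 wards in large units adds variance 0.122 × 0.878 = 0.107, so R² = 0.107/1.107 = 9.7%. The formula in step 3 then gives 3.9%, in line with the simulated 4.0%.

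**5. How large the large-unit stratum can be.** If all wards of each unit are among the 75, x units with at least five wards need 5x + (38 − x) ≤ 75, so x ≤ 9. At most 9 of 38 units lie in the upper stratum.

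**The case against.** The statistical analysis plan and full protocol are not shown, the article never says that baseline is the sole covariate, and a full covariate list is often left to the plan. The analysis plan may well contain the stratum term. Even so, the article specifies the model twice with one covariate and names tests that cannot be adjusted. The published analysis can be judged as it stands.

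The primary model already adjusts for the same ward's score 12 months earlier, which may absorb much of any size effect. The mismatch also arises only if allocation was restricted within strata, for example by blocking, which the article does not describe. Both points stand. They limit the size of the problem and are why the conclusion is conditional.

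A reader might infer three stronger things, none of which the document supports:

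- *That the test is invalid or the estimate biased.* Omitting a balanced stratifier makes the test conservative; it does not inflate type I error or bias the estimate.
- *That recruitment cycle must be in the model too.* The annual cycle is when allocation took place, not a declared stratum, and the article reports no secular trend in QELS. Nor is a cycle term clearly free: in the simulation with no size or cycle effect, adding it lowered power from 77.4% to 73.2%.
- *That stratum terms deal with large units contributing several wards to one arm.* That is clustering by randomised unit. At an assumed intraclass correlation of 0.3, simulated type I error stayed at about 11 to 12% with or without size and cycle terms.

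**Conclusion.** The stated analysis leaves out the trial's one declared stratification factor. The consequence is small and depends on unit size predicting the outcome beyond the baseline score. In that case the test is mildly conservative and some precision is lost: 4.0% against 4.8% type I error and 71.5% against 75.9% power at an assumed effect of one residual SD, and almost nothing if size is unrelated to outcome. There is no bias, and 54 and 60 wards stand. These sizes rest on an assumed size effect, an assumed distribution of wards over units, independent wards and allocation balanced within strata, since the article gives no data on any of them. This is a nearly free improvement, not a threat to the trial's conclusions.

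**What to change.** - **Primary outcome.** Add unit size (up to four against more than four wards, as used in the randomisation) as a fixed effect to the ANCOVA, beside the baseline score.
- **Staff- and patient-level secondary outcomes.** Add the same fixed effect to the multilevel models.
- **Continuous ward-level secondary outcomes.** Use a regression adjusted for baseline (where measured) and unit size in place of the unadjusted t-test or Mann–Whitney test.
- **Recruitment cycle.** Optional. If it is to be included, fix that choice before analysis and do not let it depend on cell counts seen in the data.
- **Clustering of wards within units.** Address it separately; the changes above do not correct it.

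The cost is a few lines in the analysis section and one degree of freedom per model. The Status of the trial section reports that data cleaning was still in progress, so the change could be made before analysis. The sample-size text needs no revision on this account.
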